#### Analyses

Data will be summarised and reported in accordance with Consolidated Standards of Reporting Trials (CONSORT) guidelines for randomised controlled trials [24], and we will use intention-to-treat analyses as the primary analysis. Hierarchical regression models will be used to estimate the treatment effects (with 95 % confidence intervals), as they allow us to account for the hierarchical data structure i.e. participants nested within exercise groups. We will estimate the group effects in the trial by entering the group variable into the hierarchical model as a random effect. If the group effects estimate is negligible, then multiple linear regression will be used to estimate treatment effects. The models will adjust for those covariates (age, gender, centre, and baseline ADAS-cog) which were considered to be most important in the light of clinical input. In addition we will estimate treatment effects over the 12-month time period using longitudinal models. Prespecified subgroup analyses looking at pre-randomisation variables of severity of cognitive impairment (sMMSE ≥20 and <20), type of dementia, physical performance and gender will be conducted using formal tests of interaction [23].

At the beginning of each exercise class, the physiotherapist sets aerobic exercise and resistance exercise targets specific to each participant, and then marks at the end of the class if the target was achieved. We refer to the targets set for each participant as the prescribed dose. Dose achieved will be described in two ways: (1) the percentage of the DAPA physiotherapist prescribed minutes of aerobic exercise at moderate intensity or harder that a participant achieved over the course of the DAPA exercise sessions, and (2) the percentage of the DAPA-prescribed resistance exercise dose a participant achieved over the course of the DAPA exercise sessions. For both definitions of dose, we will investigate the association between percentage prescribed dose achieved and the change in cognition by observing a simple scatter plot and then using linear regression models (unadjusted and adjusted). This will not equate to a dose–response analysis, as the dose has not been experimentally determined.

Complier average causal effect (CACE) analysis will be used to assess the effect of compliance with the intervention on the primary outcome [27]. The primary analysis will use participant-reported data. In the situations where we have collected proxy data routinely, we will undertake sensitivity analyses using these data.

The final anonymised data set will be accessible to all study members after data lock. The Chief Investigator will assume overall responsibility for the data report, and will have full access to the trial data set. There are no contractual agreements that limit access for investigators. The analysis plans described here will be finalised and approved by the Trial Steering Committee and Data Monitoring Committees prior to data lock.

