### Baseline assessment

The standardised Mini-Mental State Examination (sMMSE) [5] will be carried out immediately after consent is obtained, as a screen to ensure that the participant is eligible. We will then collect demographic and descriptive data on the participants including age, gender, marital status, ethnicity, educational attainment, employment status, and type of dementia (vascular, Alzheimer’s or mixed). In addition, we will collect the pre-randomisation (baseline) values for the outcomes to be collected during the follow-up phase of the trial (see Table 1).

**Table 1 Tab1:** Outcome measures taken at baseline, 6-month and 12-month time points

	Domain	Measure	Data supplied by
Primary	Cognition	Alzheimer’s Disease Assessment Scale-cognitive subscale (ADAS-cog) [6]	Participant (rating self)
Secondary	Function	Bristol Activities of Daily Living scale [8]	Carer (rating participant)
	Health-related quality of life	Euro-QoL (EQ-5D) [10]	Participant (rating self)
		Euro-Qol (EQ-5D)	Carer (rating self)
		Euro-Qol (EQ-5D) proxy	Carer (rating participant)
	Dementia quality of life	Quality of Life in Alzheimer’s Disease (QoL-AD) [9]	Participant (rating self)
		Quality of Life in Alzheimer’s Disease (QoL-AD) proxy	Carer (rating participant)
	Behavioural symptoms	Neuropsychiatric Inventory (NPI) [11]	Carer (rating participant)
	Carer burden	Zarit Burden Interview (ZBI) [12]	Carer (rating self)
	Health and social care usage to inform the health economics analysis	Client Services Receipt Inventory (CSRI) [13]	Participant with carer where possible (rating participant)

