### Randomisation/masking

The unit of randomisation is the individual patient. Randomisation will be stratified by site and dementia severity (moderate or mild). Dementia severity is defined as moderate for those with an sMMSE >10 but <20, and as mild dementia for those with an sMMSE ≥20. Participants will be randomised to (1) usual practice care, or (2) usual practice care plus exercise intervention. Randomisation will be 2:1 in favour of the intervention group, to allow exercise groups to be assembled in a shorter period of time. As a result, participants are less likely to withdraw between randomisation and the exercise classes commencing, are not kept waiting excessively long periods between randomisation and treatment provision, and the baseline measures are made close to the exercise classes commencing.

The random allocation sequence will be generated by an independent statistician using a computerised random number generator, and implemented by a central telephone registration and randomisation service at the Warwick Clinical Trials Unit (WCTU).

Research clinicians (registered nurses or allied health professionals) will register participants after obtaining consent, confirming eligibility and undertaking a baseline assessment. Once registered, the allocation will be generated, and the WCTU DAPA trial team will inform the participant of their allocation and make arrangements for treatment referral. Neither intervention providers nor participants can be masked to treatment allocation. If a research clinician becomes unmasked then follow-up assessments will be conducted by different research workers, and all study personnel involved with data entry, follow-up assessments, management and analysis will be masked until the final analysis is complete.

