### Choice of outcome measures

The primary outcome will be the global cognition score of the Alzheimer’s Disease Assessment Scale-cognitive subscale (ADAS-cog) [6], measured at 12-month follow-up. This instrument has 11 standard items, and additionally the maze and number cancellation optional items, which will be reported separately. It takes about 30–40 minutes to administer. The score ranges from 0 to 70, with higher scores indicating greater impairment. Cognitive deficits are central to dementia and widely understood as the most important treatment target. In the original study protocol, standardised Mini-Mental State Examination (sMMSE) [5] was the measure of cognition used. It was replaced by ADAS-cog on the recommendation of the TSC and DMEC because the latter is widely considered the gold standard primary outcome in treatment trials for dementia, with relatively well-established treatment effect sizes [7], and has superior sensitivity to change and hence is a more efficient instrument from the point of view of experimental design.

Secondary outcomes have been chosen to reflect the broad impact of dementia: on function, on behaviour, on quality of life, on economic costs, and on the carer. Where possible, we have chosen instruments which are dementia-specific, well-validated and not excessively burdensome. Secondary outcomes are detailed in Table 1.

We will use the Bristol Activities of Daily Living scale (BADL) [8]. This carer-rated instrument is dementia-specific and covers 20 activities of daily living. It is sensitive to change and widely used in clinical trials. Quality of life is widely considered important in dementia. We will collect data using the Quality of Life in Alzheimer’s Disease (QoL-AD) [9], a 13-item dementia-specific scale which can be completed by a carer or participant (both will be collected during the DAPA trial). We will also collect the EuroQol EQ-5D [10], a 5-dimension generic (i.e. not dementia-specific) measure of health-related quality of life. This will be collected from both the participant’s and the carer’s perspective. EuroQol EQ-5D allows a calculation of health utilities for application in economic evaluations.

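### The listed model covariates leave out dementia severity, one of the two factors on which randomisation is stratified

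*Protocol article*

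**What the plan says.** On design, the Randomisation/masking section states: "Randomisation will be stratified by site and dementia severity (moderate or mild"). The strata are then defined: "Dementia severity is defined as moderate for those with an sMMSE >10 but <20", with mild dementia at 20 or above.

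On analysis, the Analyses section begins: "Hierarchical regression models will be used to estimate the treatment effects". It then gives one covariate list: "The models will adjust for those covariates (age, gender, centre, and baseline ADAS-cog) which were considered to be most important". Severity returns later in the same paragraph, as a subgroup variable with the same cut at 20: "Prespecified subgroup analyses looking at pre-randomisation variables of severity of cognitive impairment". The Usual care section explains why centre is in the models: care varies between centres, so randomisation is stratified within centre and the analysis adjusts for it. There is no matching statement for severity.

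On baselines, the Baseline assessment section states: "we will collect the pre-randomisation (baseline) values for the outcomes to be collected during the follow-up phase of the trial". Table 1 lists these outcomes: ADAS-cog, BADL, EQ-5D, QoL-AD, NPI, ZBI and the CSRI. The Analyses section gives no separate covariate list for the secondary outcomes.

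**The concern.** When randomisation is stratified on a prognostic factor, the arms are balanced on it by design, and the treatment estimate varies less than it would under simple randomisation. A model that omits the factor leaves its contribution in the residual. The reported standard error is then too large for the design used, and the test runs below its nominal level. The usual remedy is to include every stratification factor in the model. This article does so for site but not for severity.

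The omission is also awkward within the plan. A standard interaction model for the severity subgroup contains the severity main effect, so the subgroup model would respect the stratification while the main model would not.

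A second, weaker point comes from the same sentence. The list names baseline ADAS-cog and is not tied to one outcome. It therefore does not tell the reader which baseline goes into the model for BADL, NPI, ZBI, QoL-AD or EQ-5D.

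**Working it through.** **1. The plan's own figure.** Inputs from the Sample size section: difference 2.45, SD 7.8, alpha 0.05 (two-sided reproduces the result), power 80%, allocation 2:1.

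- Control arm: 1.5 × (7.8 × (1.960 + 0.842) / 2.45)² = 119.3, rounded to 120. Total: 3 × 120 = 360, as stated.
- Design effect: 360 × 1.04 = 374.4, rounded to 375, as stated.
- Loss to follow-up: 375 / 0.80 = 468.75, stated as 468 (312 + 156).

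No covariate enters this formula, so the planned size does not depend on the covariate list.

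**2. Stratification factors against covariates.**

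| Stratification factor | In the listed covariates? | Elsewhere in the analysis |
|---|---|---|
| Site | Yes, as centre | – |
| Severity (sMMSE cut at 20) | No | Subgroup interaction only |

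**3. Cost for the primary outcome.** All correlations here are assumptions. With sMMSE reversed so that higher is worse, let ρ be its correlation with baseline ADAS-cog (0.6, 0.7, 0.8), r the baseline to 12-month ADAS-cog correlation (0.7, 0.8), and m the correlation of sMMSE with 12-month ADAS-cog (0.5, 0.6, 0.7). That makes 18 scenarios. The cut is placed 0.25 SD from the mean, which puts about 40% of participants in one stratum (also an assumption).

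Dichotomising multiplies correlations by a = φ(0.25) / √(0.401 × 0.599) = 0.387 / 0.490 = 0.789. The residual variance with baseline ADAS-cog alone is 1 − r². Adding the stratum removes a further

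d = (a·m − a·ρ·r)² / (1 − a²ρ²),

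and the interval without the stratum is wider by the factor √[(1 − r²) / (1 − r² − d)].

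- ρ = 0.7, r = 0.7, m = 0.6: d = 0.011, and √(0.510 / 0.499) = 1.011, or 1% wider.
- ρ = 0.6, r = 0.7, m = 0.7 (largest loss): d = 0.063, and √(0.510 / 0.447) = 1.068, or 7% wider.
- All 18 scenarios: 15 lie between 0 and 3%; the other three are 4%, 6% and 7%.

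A simulation of the same scenarios gives the same figures to within 0.1 percentage point.

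If stratification balances severity closely, a standard error overstated by 3% makes a nominal 5% test run at 2 × [1 − Φ(1.96 × 1.03)] = 4.4%. At 6.8% it runs at 3.6%. The error is on the conservative side.

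**4. Secondary outcomes, if the list were applied literally.** Let r be the correlation of an outcome with its own baseline (0.5 to 0.8) and c its correlation with baseline ADAS-cog (0.2 to 0.4), both assumed. Using baseline ADAS-cog in place of the own baseline widens the interval by √[(1 − c²) / (1 − r²)]. The square of this is the ratio of sample sizes needed.

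| r | c | Interval ratio | Sample size ratio |
|---|---|---|---|
| 0.5 | 0.4 | √(0.84 / 0.75) = 1.06 | 1.12 |
| 0.6 | 0.3 | √(0.91 / 0.64) = 1.19 | 1.42 |
| 0.7 | 0.3 | √(0.91 / 0.51) = 1.34 | 1.78 |
| 0.8 | 0.2 | √(0.96 / 0.36) = 1.63 | 2.67 |

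**The case against.** On severity, the defence is that baseline ADAS-cog is already in the model. It is a continuous score from 0 to 70 for global cognition, while the stratum is a two-level cut of another cognitive test, so most of the stratum's prognostic information is already used. This stands, and it is why the loss in step 3 is small. It does not explain the omission: the article gives a reason for adjusting for centre and none for leaving out the other stratification factor.

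On secondary outcomes, a reader might infer that they are to be adjusted for baseline ADAS-cog instead of their own baselines, and that their intervals will be needlessly wide. The case for that reading is that the list is given for the models in general, whereas the CACE analysis is expressly confined to the primary outcome. The documents do not support it as a finding. The analysis paragraph names no secondary outcome. Baseline ADAS-cog is the primary outcome's own baseline, so the list may describe only the primary model. Nothing calls the list exhaustive. The article also refers to a full protocol, and says that the analysis plans will be finalised before data lock. Outcome-specific covariates commonly sit in such documents, which are not shown here. What remains is an ambiguity that one clause would remove.

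**Conclusion.** The severity point holds, as a mismatch between design and analysis with a small cost. The listed covariates omit one of two stratification factors. For the primary outcome the interval would be roughly 0 to 3% wider in most assumed scenarios and at most 7% wider. The estimate is not biased, the type I error is not inflated, and the 360 / 375 / 468 sample size is unchanged. These percentages rest on assumed correlations and an assumed split between strata. The omission itself is read directly from the text.

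The range of 6 to 63% for secondary outcomes shows what a literal application of the list would cost. It is not an estimate of what the trial will do.

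**What to change.** Before the analysis plan is finalised, replace the covariate sentence with wording such as: all models adjust for the stratification factors (centre and sMMSE stratum, 20 or above versus below 20), age, gender and the baseline value of the outcome being analysed; for the primary outcome that baseline is ADAS-cog. Continuous sMMSE could be used in place of the stratum.

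The change takes one sentence and one further degree of freedom in each model. It needs no new data, because sMMSE is recorded at screening and baseline values of the follow-up outcomes are already collected. The sample size does not change.

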### Economic evaluation

The most significant formal costs associated with dementia are the costs of social and long-term care [28]. Hospitalisation costs are also likely to occur, particularly related to falls and injuries [29]. The economic evaluation will therefore focus on the following major components of costs: NHS primary and secondary care, local authority care, the costs to other agencies or organisations, costs associated with institutional care and home care support. Intervention costs will reflect the costs necessary to implement the DAPA physical activity, including development and training, overheads, equipment, and staff-related expenses.

Two economic evaluations will be undertaken – first, *a within-trial evaluation*, and second, *a decision analytic-based cost-effectiveness model*. Both will be used to estimate the expected incremental cost per quality-adjusted life-year (QALY) gained for the DAPA interventions in comparison to best practice usual care. For both analyses, the primary perspective will be that of the UK NHS and personal social services. The potential impact of adopting a societal perspective on incremental cost-effectiveness ratios will be tested in sensitivity analyses using data on informal and indirect costs provided by carers at 6 and 12 months.

The within-trial analysis will compare the costs and outcomes between the study arms at the end of follow-up. The primary outcome measure will be the quality-adjusted life-year (QALY). Health-related quality of life (HRQoL) will be estimated using responses to the EuroQol EQ-5D [10] obtained from participants and their carers (participant self-report, carer proxy report and carer self-report). The primary analyses will be conducted using the EQ-5D responses obtained from the participants. Nevertheless, differences between participant and carer assessments of participant HRQoL will be acknowledged through sensitivity analyses. Utility weights will be taken from the UK General Population tariff for the EQ-5D [30, 31]. Unit costs will be taken from national databases including the NHS reference costs and the Personal Social Services Research Unit (PSSRU) costs of health and social care. Where national unit cost estimates are not available unit costs will be estimated using established accounting methods in consultation with NHS Trusts recruiting to the study. In line with current recommendations for best practice in economic analyses, costs and outcomes will be discounted at 3.5 % per annum [32]. Probabilistic sensitivity analysis will be undertaken using the non-parametric bootstrap. We will use the CSRI as a framework for resource data capture [33].

The decision analytic cost-effectiveness analysis model will use a lifetime time horizon to capture the full impact of any mortality and health-related quality of life differences on the long-term cost-effectiveness of the exercise intervention. It is likely that the model will have a semi-Markov structure to capture the time trend in the underlying risk of mortality, health-related quality of life, and costs of care. The methods for estimating health-related quality of life and utility, unit costs and discounting will be the same as for the within-trial analysis.

Probabilistic sensitivity analyses will be undertaken using Monte Carlo simulation techniques. The outputs reported from the analysis will be the same as for the within trial analysis.

### Qualitative study

We will conduct a qualitative study in parallel to the trial, the aim of which is to provide insight into participants’, carers’ and staff experiences of taking part in the experimental intervention. Semi-structured interviews with participants and carers and observations of the exercise classes will be carried out by a researcher trained and experienced in qualitative research methodologies. Observations will take place near the beginning, middle and towards the end of the supervised part of the intervention. We will conduct the interview study in two sections. The first section will interview participants as they experience the moderate to hard intensity training. We will recruit a second, separate sample and interview participants approximately 4 months after they have finished the supervised part of the intervention.

It is possible that some participants may have problems recalling their experiences. In those instances the focus of the interview will be on their current experiences of exercise. For those participants able to recall their experiences of the supervised part of the intervention interviews will seek to capture their experiences of taking part in both the supervised and unsupervised parts of the intervention. Current evidence suggests that doing research interviews with people with cognitive impairments presents a number of obstacles; these include short-term memory problems, difficulties in abstract thinking and expressive language, a lack of insight and awareness of their diagnosis, and damage to their sense-of-self related to their experiences of diagnosis and symptoms of dementia [34]. It is suggested that obstacles may be overcome by the interviewer adopting an attitude that assumes the person with dementia has something valuable to say, by listening carefully, accepting the interviewee as they are and with an openness to understand them. The deployment of strategies to minimise or overcome dementia-related obstacles include: taking a case-specific approach by taking the time to meet interviewees before the formal interview in order to build rapport and gauge expressive skills, being comfortable with long pauses and the expression of strong emotions, avoiding the use of complex concepts and adjusting the language to align with participants’ language, use of photographs as a memory aid and use of direct interview styles where expressive skills are very limited [34, 35]. The researcher undertaking the interviews has experience and training around these issues.

Interviews with carers will include a focus on participants’ and carers’ experiences of taking part in the supervised and unsupervised parts of the intervention and their experiences of living with dementia. We will interview participants until we feel confident that we have reached data saturation. Based on our previous experiences we anticipate that we will interview approximately 20 participants and their carers. Sampling will be purposive and will be aimed at reflecting the population of the intervention arm of the trial in relation to gender, ethnicity and social class. Pseudonyms will be used and any other identifying information will be anonymised to ensure participants’ confidentiality is maintained. Interview transcripts and field notes will be uploaded into NVivo (QSR International Pty Ltd, Melbourne, Australia), a computer program for qualitative data, to assist with data management and analysis.

Our approach to data analysis will be thematic and will broadly follow the principles of grounded theory [36]. This requires a constant moving back and forth within and across field notes and transcripts and starts from the first interview and continues throughout the data collection period and beyond. A thematic analysis involves identifying, describing, analysing, interpreting and reporting repeated patterns or themes and categories within participants’ transcripts using a deductive and inductive approach. A theme captures important meanings across participants in relation to the research question and represents some level of patterned response or meaning across a data set and the relevant research literature [37]. Transcripts will be analysed by the researcher carrying out the interviews and, to ensure rigorous analysis, a second senior researcher will independently analyse approximately 20 % of the transcripts [37]. These two researchers will meet to discuss the differences and similarities between the transcripts and their own interpretations of them will be explored. Discussion of the analytic process and its findings will be shared within the wider research team thereby enabling an opportunity for critical reflection and further analytic refinement. Disagreements regarding the identification, description, analysis or interpretation of themes will be resolved through discussion and if necessary further analysis.

